## 9. METHODS

### 9.1 Study algorithms

#### 9.1.1 TME-study

[figure not shown]

**Fig 1.** Study layout for impacted third molar extraction (TME) participants. The general timelines of the impacted third molar extraction (TME) study. Information day (green bar) where participants are informed about the study. The day of surgery (red), the follow-up phone call (yellow; 2 weeks  $\pm$  3 days] after TME), the first examination day (Day 1; dark blue; 4 weeks  $\pm$  3 days]) and the second examination day (Day 2; blue; exactly 7 days after Day 1).

[figure not shown]

**Fig 2.** Test-algorithm Day 1/2 for TME-participants and Day 2/4 for BI-participants with superimposed naloxone plasma-concentration curves. Median plasma-concentration (red) with 95% CI (dashed black lines) during a three-step target-controlled-infusion (TCI). Naloxone is given at step one with 0.25 mg/kg, step two 0.75 mg/kg and step three 2.25 mg/kg. Yellow timeline columns represent ratings with Clinical Opiate Withdrawal Scale (COWS) and blue columns indicate sensory testing (pain during rest, movement and 100 kPa pressure; pressure algometry; secondary hyperalgesia area). **BL** = baseline assessments (-20" to -8"; please, observe for BI-participants baseline assessments are made - 2hrs 20"

to – 2hrs 8" before start of TCI); **S1** = step one assessments (15" to 25"); **S2** = step two assessments (39" to 49"); **S3** = step three assessments (65" to 75").

At the follow-up phone call 2 weeks ( $\pm$  3 days) after surgery any questions the participant may have regarding the study will be discussed. The post-surgical pain intensity and signs of post-surgical complications will be penetrated (swelling, pain, fever, malaise, excessive lymph-node swelling).

The study drug (naloxone or placebo) will be given in a randomized fashion on the examination days, Day 1 and Day 2. Day 1 takes place 4 weeks ( $\pm$  3 days) after surgery. Day 1 and Day 2, separated by exactly 7 days, are at Department of Neuroanaesthesia 3042, Rigshospitalet (Fig. 1). Procedures on Day 1 and Day 2 will be performed by a physician and a research-nurse.

The agenda for the examination days are:

#### 9.1.2.1.1 Day 1/Day 2

- Assessment of inclusion and exclusion criteria
- The participant gives his informed consent (only Day 1)
- The participant fills out the Hospital Anxiety and Depression Scale (HADS; only Day 1)
- The participant fills out the Pain Catastrophizing Scale (PCS; only Day 1)

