## **11. DRUG ADMINISTRATION**

### **11.1 Target-controlled-infusion (all participants)**

The target-controlled-infusion (TCI) algorithm (Fig. 2) was calculated by the software NONMEM (7.3 ICON Development Solutions, Manchester, U.K. [property of UCSF, U.S.]), using computer simulations based on a population-kinetic model with 2,000 simulated administrations distributed on 10 subjects (Table 1). Thus a total dose of 3.25 mg/kg of naloxone will be administered in a step-wise approach for 75 minutes as follows (Table 1): In the first minute (0-1 min) a bolus of 0.02 mg/kg will be given followed by an infusion of 0.23 mg/kg during 24 minutes (1-25 min). Afterwards (25-26 min) a bolus of 0.06 mg/kg will be administered followed by a 24-minute infusion of 0.69 mg/kg (min 26-50). Finally a bolus of 0.18 mg/kg (50-51 min) will be given followed by a 24-minute infusion of 2.07 mg/kg (51-75 min). With this administration algorithm estimated naloxone plasma concentrations (median [95% limits]) of 344 ng/ml [130;567], 1,059 ng/ml [400;1,752] and 3,196 ng/ml [1,205;5,276] at time intervals 15-25 min, 40-50 min and 65-75 min, respectively, are achieved (Fig. 2). For TME-participants an identical infusion-algorithm will be used for the placebo infusion. All outcomes for TME-participants will be assessed before infusion and 3 times during infusion at the above mentioned

time intervals. In BI-participants blood-samples for pharmacokinetic outcomes are obtained at specified time-points during and after the TCI (cf. 9.1.2).

|                   | time (min)   | dose (mg/kg) | dose/70 kg (mg) | volume/70 kg (ml) | ml/min/70 kg |
|-------------------|--------------|--------------|-----------------|-------------------|--------------|
| Bolus 1    | 0-1   | 0.02         | 1.40            | 0.35              | 0.35         |
| Infusion 1 | 1-25  | 0.23         | 16.10           | 4.03              | 0.17         |
| Bolus 2    | 25-26 | 0.06         | 4.20            | 1.05              | 1.05         |
| Infusion 2 | 26-50 | 0.69         | 48.30           | 12.08             | 0.50         |
| Bolus 3    | 50-51 | 0.18         | 12.60           | 3.15              | 3.15         |
| Infusion 3 | 51-75 | 2.07         | 144.90          | 36.23             | 1.51         |
| TOTAL      |              | 3.25         | 227.50          | 56.88             |              |

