### 13. STATISTICAL ANALYSES

#### 13.1 Sample size calculations

##### 13.1.1 TME-participants

Sample size calculations are based on following assumptions and estimations (abbreviations: BL = baseline; NX = naloxone; PL = placebo; TCI = during target-controlled-infusion):

1. a primary outcome based on a summed measure (SM) of resting pain (RP), masticatory pain (MP; (movement-related) and pressure-evoked pain (PM; pressure algometry [100 kPa]).  $NRS_{SM} = NRS_{RP} + NRS_{MP} + NRS_{PM}$ .
2. the summed pain intensities (SPIs) are calculated as: (BL-SPINX) and (TCI-SPINX), and, (BL-SPIPL) and (TCI-SPIPL), where (TCI-SPI) indicates SM-value at highest obtainable TCI-step (Fig. 2).
3. the summed pain intensity differences (SPIDs) are the differences: **SPIDNX** = (TCI-SPINX) – (BL-SPINX) and **SPIDPL** = (TCI-SPIPL) - (BL-SPIPL)

4. the mean [SD] BL-pain intensities are estimated to be: resting pain 1 [1] NRS-units; movement related pain 2 [2] NRS-units; pressure evoked pain 4 [2] NRS-units.
5. the mean [SD] summed BL-pain intensity (BL-SPI) is estimated to be 7 [4.1] NRS-units (Table 2).
6. the minimal relevant SPID-difference, calculated as  $\Delta SPID = SPID_{NX} - SPID_{PL}$  is estimated to be 5 (NX-group: RP = 4; MP = 5; PM = 7 [total 16]/PL-group: RP = 2; MP = 4; PM = 5 [total 11]) corresponding to a  $\Delta SPID\% = 45\%$ .
7. the design is a placebo-controlled, randomized, double-blind, crossover study
8. the significance level  $\alpha$  is set to 0.01 and the power is set to  $= 0.90$  ( $\beta = 0.10$ )

The total number of individuals estimated to be included in the study is calculatedE to be 14 (effect size 1.2). Using the range of variances in Table 2, it can be calculated that the number of individuals ranges from 9 to 19, with effect sizes of 1.7 to 1.0, respectively.

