## 13.2 Data processing

### 13.2.1 TME-participants

To test if data is normally distributed, residual plots and the Kolmogorov-Smirnov test will be used (SPSS 20.0, Chicago, IL, USA; MedCalc Software: version 12.07.0.0; Mariakerke, Belgium). In case of non-normal data distribution, primarily a logarithmic transformation is tried or secondarily a Box-Cox transformation will be attempted for normalization of data.

The primary outcome  $\Delta\text{SPID}$  ( $\text{SPID}_{\text{NX}} - \text{SPID}_{\text{PL}}$ ) is analyzed by one-way repeated measures ANOVA ( $\Delta\text{SPID}$ : dependent variable; TCI-steps: independent variable) or a corresponding non-parametric analogue (Friedman test), as appropriate. Paired  $t$ -test or Wilcoxon rank sum test will be used, as appropriate for inter-group comparisons.

A mixed model with random effect for subject and fixed-effects for the factors; *target-controlled-infusion* (step 1/step 2/step 3), *drug* (naloxone/placebo); *secondary hyperalgesia area* (SHA); *pressure pain threshold* (PPT); *HADS-score*; and *PCS-scores*, are used for the primary outcome  $\Delta\text{SPID}$  ( $\text{SPID}_{\text{NX}} - \text{SPID}_{\text{PL}}$ ). Non-significant ( $P > 0.05$ ) factors, beginning with interactions, are excluded until all included factors attain significance. Main-effects and interaction-effects are examined.

The risk of type I error is reduced by setting a significance level of 0.01 ( $\alpha$ ). A power of 0.90 ( $\beta = 0.10$ ) is set in order to reduce the risk of type II errors. For all statistical calculations, in which multiple comparisons are performed, Duncan's new multiple range test or Scheffé's method, as appropriate, will be used. Statistical calculations will be performed with partially un-blinded data, i.e., group A and B. When statistics have been completed, data are unblinded, into naloxone and placebo groups.

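### TME mixed model: drug can be estimated only from per-day SPID, and on that reading a subject-only random effect makes the nominal 1% drug test too liberal

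*Protocol*

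**What the plan says.** Treatment is allocated by day (section 9.1.1): "The study drug (naloxone or placebo) will be given in a randomized fashion on the examination days, Day 1 and Day 2". Each subject therefore has one naloxone day and one placebo day. Section 11.1 gives the measurements within a day: "All outcomes for TME-participants will be assessed before infusion and 3 times during infusion".

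Section 13.1.1 defines the change scores: "the summed pain intensity differences (SPIDs) are the differences" between the infusion value and the baseline of the same drug condition. Item 2 of that list takes the infusion value at the highest obtainable step.

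Section 13.2.1 (TME-participants) names three analyses:

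- a one-way repeated-measures ANOVA of ΔSPID over infusion steps;
- a paired t-test, or a Wilcoxon alternative, for comparisons between groups;
- "A mixed model with random effect for subject and fixed-effects for the factors" infusion step, drug, secondary hyperalgesia area, pressure pain threshold, HADS and PCS, with ΔSPID as the outcome.

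The only random effect named is subject. On error control the section says: "The risk of type I error is reduced by setting a significance level of 0.01".

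**The concern.** The outcome and the factor list do not fit together. ΔSPID has one value per subject and step and is already differenced over drug, so drug has no variation left to explain. Keeping drug as a factor forces the outcome back to SPID, with one value per subject, day and step.

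A second problem then appears. Drug changes only between days, so its proper error term is the variation between the two days of a subject. The three SPIDs of a day all subtract the same baseline and carry its error, so they resemble each other more than they resemble the other day's values. A subject intercept gives same-day and different-day pairs the same correlation. The model therefore treats the three step scores as nearly separate replicates of the drug contrast, and the standard error is too small.

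Drug is the effect the TME study exists to test, and this is the only named model with a drug term. Section 13.1.1 also ends the study if the interim analysis rejects the null hypothesis, without naming the test. If the mixed model were used there, the study could stop on an inflated result.

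**Working it through.** **The plan's own figure.** Inputs from section 13.1.1 and Table 2: difference 5, SD 4.12 (correlation 0.5 between pain components), α 0.01, power 0.90. Effect size = 5/4.12 = 1.21. A two-sided paired t-test (noncentral t) gives n = 14, as stated. Effect sizes 1.7 and 1.0 give 9 and 19, also as stated. The study was thus sized on one difference per subject, with n − 1 = 13 degrees of freedom.

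**Model on the per-day reading.** For a subject with effect u, on one day, at step j:

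SPID_j = u + e_j − e_0, with var(e_j) = s² and var(e_0) = r·s².

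The ratio r is an assumption; the protocol gives no value for it. The correlation of 0.5 in Table 2 is between pain components, not between steps, and does not supply it.

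**Degrees of freedom, n = 14.** There are 14 × 2 × 3 = 84 values. Removing the mean (1), drug (1), step (2) and subject (13) leaves 67 = 5n − 3 for the residual. Of these, n − 1 = 13 belong to subject-by-drug, that is subject-by-day, and 4n − 2 = 54 to the rest.

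**Expected mean squares under no drug effect.**

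- The error variance of a day mean is s²/3 + r·s². Multiplied by 3 steps, the subject-by-day mean square has expectation (1 + 3r)s². This is the right yardstick for drug.
- The other 54 degrees of freedom have expectation s².
- The subject-only model pools them: [13(1 + 3r) + 54]s²/67.

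**At r = 1.** Right yardstick 4s². Pooled: (13 × 4 + 54)/67 = 106/67 = 1.58s². Ratio 4/1.58 = 2.53. The 1% critical value of 2.65 then acts like 2.65/√2.53 = 1.67, which corresponds to a two-sided error of roughly 10%. At n = 30 the pooled value is (29 × 4 + 118)/147 = 1.59s² and the ratio 2.51, so a larger trial does not help.

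**Other ratios, n = 14,** with simulated rejection rates (40,000 null trials each, nominal 1%):

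| r | Right yardstick | Pooled | Variance understated by | Rejection rate |
|---|---|---|---|---|
| 1 | 4.00 s² | 106/67 = 1.58 s² | 2.53 | 10.5% |
| 0.5 | 2.50 s² | 86.5/67 = 1.29 s² | 1.94 | 6.2% |
| 0.25 | 1.75 s² | 76.75/67 = 1.15 s² | 1.53 | 3.6% |
| 0.1 | 1.30 s² | 70.9/67 = 1.06 s² | 1.23 | 2.0% |
| 0 | 1.00 s² | 67/67 = 1.00 s² | 1.00 | about 1% |

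A repeat simulation for this write-up agreed within simulation error. At r = 1 the rate was also about 10% at n = 18 and n = 30.

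**Further day-level correlation.** Added day-to-day variation in response gives 13% to 15%, serially correlated steps 16%, and a within-day correlation of 0.8 about 20%.

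**Comparators.** A paired t-test on one value per subject and day rejects 0.9% to 1.1% of null trials, whether that value is the day mean (equivalent, in balanced data, to adding a random day effect) or step 3 alone. The literal ΔSPID reading, testing the mean with a subject intercept on n − 1 degrees of freedom, gives 1.0%.

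**The case against.** The strongest reply is that the criticised model is not the one written. The stated outcome is ΔSPID, for which the two baselines reduce to a term constant within subject. A subject effect absorbs that term, and the error rate is 1.0%. Deleting drug from the factor list would restore consistency, and the inflation would not arise. This stands as a second way to resolve the contradiction. It does not rescue the text as it is, because the listed drug factor can be fitted only to per-day SPID.

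Second, section 13.1.1 defines SPID only at the highest obtainable step, so three SPIDs per day are inferred from the step factor and from the steps over which section 13.2.1 analyses ΔSPID. That is correct, and it is part of what needs stating.

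Third, the same section names a paired t-test, which is valid and matches the sample size. A reader might infer that the trial's 1% error rate as a whole becomes 10%. The protocol does not support that: the inflation concerns the mixed-model drug test alone. The protocol does not, however, rank the paired test above the model or say which step it uses.

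Fourth, a flat figure of 10% is tempting but rests on equal baseline and step error variances, which the protocol does not give.

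Finally, residual covariance and degrees-of-freedom methods are often left to a statistical analysis plan, and one that added a day term would settle the matter. But the protocol does fix a random effect, and the one it fixes is not enough for a drug factor.

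**Conclusion.** The point holds in conditional form. As written, outcome and drug factor are incompatible. Under the only reading in which drug can be estimated, the stated subject effect gives drug too small an error term. Any measurement error in the shared baseline pushes the error rate above 1%, so the direction is firm. The size depends on the baseline-to-step error variance ratio: about 10% at equality, about 6% at one half, and 2–4% at a tenth to a quarter, with higher rates if days differ in other ways. These figures assume independent step errors, no other named covariance structure and balanced data. They exclude any effect of the interim look or of the stepwise removal of factors. The paired t-test in the same section is unaffected.

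**What to change.** In section 13.2.1 (TME-participants), choose one of the following.

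1. State the mixed-model outcome as SPID per day and step. Specify random effects for subject and for examination day within subject, and test drug on the subject-by-day stratum with about n − 1 degrees of freedom.
2. Make the paired comparison of SPID at the highest obtainable step the primary drug test. This is the quantity in item 2 of section 13.1.1, and a paired t-test is the basis that reproduces n = 14. Use the three-step model only to describe dose response.

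In either case, name the test that the interim analysis uses. The cost is a sentence or two of wording and, under the first option, one more variance component. Intervals and p-values for drug become larger than the subject-only model would give, which is their correct size. The sample size calculation is unaffected, since it already rests on one paired difference per subject.

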#### *9.2.6 Pressure pain threshold (TME-participants)*

Pressure pain threshold (PPT) will be assessed using an electronic pressure algometer (Algometer, Somedic AB, Sweden). The pressure algometer employs a 1-cm^2 circular probe, which is applied manually, perpendicularly to the skin with increasing pressure at a rate of 1-2 kPa/s. The assessment area will include the point of maximum pain. PPT assessments will be performed at baseline (-20 min to -8 min; Fig. 2) and during infusions (15 min to 25 min; 39 min to 49 min; 65 min to 75 min) at the surgical site and at the mirror-site in the contralateral groin. The participants interrupt the stimulation by pushing a button when the pressure becomes painful, and the investigator then stops the stimulation. The cut-off value is 350 kPa. Values exceeding the cut-off are designated 351 kPa.

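### Both primary-outcome mixed models drop terms at P > 0.05 with no decisive test named, and the TME model may adjust for responses to the drug

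*Protocol*

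**What the plan says.** Section 13.2.1 (TME-participants) gives the primary outcome ΔSPID two analyses. The first is a one-way repeated-measures ANOVA over infusion steps (or Friedman), with a paired t-test or Wilcoxon test for comparisons. The second is a mixed model with a random subject effect and the factors infusion step, drug, SHA, PPT, HADS and PCS. In that model, factors with P > 0.05 go: "factors, beginning with interactions, are excluded until all included factors attain significance". Main effects and interactions are both examined. The section does not say which analysis decides.

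The next paragraph states: "The risk of type I error is reduced by setting a significance level of 0.01". For multiple comparisons, "Duncan's new multiple range test or Scheffé's method, as appropriate, will be used".

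The BI section, also numbered 13.2.1, repeats the elimination rule and the 0.01 statement. Its factors are SHA, sensitizer group, infusion step, HADS and PCS, for the outcome ΔSHA between sensitizer groups.

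On timing, section 9.2.6 says "PPT assessments will be performed at baseline (-20 min to -8 min; Fig. 2) and during infusions". Section 9.1.1 repeats the baseline battery, which includes SHA, at each infusion step. HADS and PCS are marked as pre-infusion only in section 3.2.1. Section 2 gives the first aim as testing whether naloxone brings back pain and hyperalgesia.

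**The concern.** There are three linked problems.

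1. **Two thresholds and no decisive test.** A term counts as significant for retention at 0.05, while the stated level is 0.01. Several drug or group terms are examined after data-driven selection, and any of them could be reported as the finding. The term of interest can itself be removed.
2. **Possible adjustment for drug responses.** If the SHA and PPT values in the TME model come from the infusion, they are measured after dosing and are expected, on the trial's own hypothesis, to change with naloxone. The adjusted drug term then no longer estimates the total effect of naloxone on pain.
3. **Models that do not match their outcomes.** ΔSPID is SPID on naloxone minus SPID on placebo, so drug has no levels left to enter as a factor. In BI, SHA is a factor for an outcome computed from SHA, and sensitizer group has already been subtracted out of the group difference.

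At stake is whether a reported P value means what the 0.01 statement suggests, with 14 evaluable TME subjects and 40 BI subjects.

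**Working it through.** **The plan's own figure.** Section 13.1.1 gives a minimal relevant ΔSPID that "is estimated to be 5 (NX-group: RP = 4; MP = 5; PM = 7 [total 16]/PL-group" total 11, an SD from "summed BL-pain intensity (BL-SPI) is estimated to be 7 [4.1] NRS-units (Table 2" (4.12 in Table 2 at correlation 0.5), α 0.01 and power 0.90, and a sample size calculated "to be 14 (effect size 1.2").

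- d = 5 / 4.12 = 1.21.
- Exact two-sided paired t-test at 0.01: N = 14, power 0.914.
- d = 1.7 gives 9 and d = 1.0 gives 19, matching the stated range. A one-sided test would give 12.

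So the sample size corresponds to one unadjusted two-sided paired test at 1%, not to the mixed model with elimination.

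**Error under the null, TME.** Simulation: 14 subjects × 2 sessions × 3 steps, SPID as response (because ΔSPID cannot carry a drug factor), random subject intercept, backward elimination at P > 0.05, five drug interactions, covariates not moved by the drug, 3,000 runs per row. The SPID–covariate correlations are assumptions.

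| Assumed correlation | Drug main effect, P < 0.01 | Drug main effect, 0.05 | Any drug term, P < 0.01 | Any drug term, 0.05 | Fixed drug + step model, P < 0.01 |
|---|---|---|---|---|---|
| 0 | 0.9% | 5.5% | 6.9% | 25.4% | 0.7% |
| 0.3 | 1.4% | 6.1% | 7.8% | 26.7% | 0.9% |
| 0.6 | 0.9% | 4.5% | 6.3% | 23.7% | 0.9% |

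These agree with simple arithmetic for six independent terms: 1 − 0.99⁶ = 5.9% and 1 − 0.95⁶ = 26.5%. The loss therefore comes mainly from several examined terms and the 0.05 threshold. Elimination alone adds little.

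**Error under the null, BI-type.** Ordinary least-squares simulation: 40 subjects, group, HADS, PCS and two-way interactions, 6,000 runs.

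- Group main effect at 0.01: 3.1% uncentred, 1.3% with centred covariates.
- Any group term at 0.01: 4.7% uncentred, 3.4% centred.

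This simplifies the stated model, since it has no infusion step and no random subject effect.

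**Adjusting for infusion-time SHA and PPT.** True drug effect 5, 500 runs per case. The correlation and the shift naloxone causes in SHA and PPT are assumptions, because the protocol gives neither.

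| Correlation | Shift in SHA/PPT | Adjusted estimate | Lost |
|---|---|---|---|
| 0.3 or 0.5 | none | 5.0 | none |
| 0.3 | 0.5 SD | 4.42 | 12% |
| 0.3 | 1 SD | 3.93 | 21% |
| 0.5 | 0.5 SD | 3.98 | 20% |
| 0.5 | 1 SD | 2.96 | 41% |

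The loss is (5 − estimate) / 5. The unadjusted estimate stays at about 5.0 in every case. Conversely, with no drug effect on SPID but SHA and PPT shifted by 0.5 SD (correlation 0.5, 1,000 runs), the adjusted drug test rejects at 0.01 in 31% of trials, against 1.0% unadjusted. The distortion can thus run toward zero or away from it.

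**Duncan's test.** Its familywise error can reach 1 − (1 − α)^(k−1). At α = 0.01 this is 1 − 0.99² = 2.0% for three means and 1 − 0.99³ = 3.0% for four.

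**The case against.** The best reply is that section 13.2.1 first lists an ANOVA and paired tests for ΔSPID, with no covariates and no elimination, and that the sample size matches the paired test. On that route nothing is selected or adjusted away. This is correct, and it limits the point. It does not remove it, because the section also assigns the mixed model to the primary outcome and never says which result counts.

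A reader might infer several stronger things that the protocol does not support:

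- **That elimination by itself destroys the 1% level.** For one centred main effect judged at 0.01, it does not.
- **That SHA and PPT are certainly infusion values.** The section does not say. A model by infusion step, with only HADS and PCS marked pre-infusion, makes this the likelier reading. If baseline values were meant, the adjustment concern falls away.
- **That adjustment always shrinks the effect.** The 31% result shows otherwise.
- **That power collapses.** If half of a 5-point effect were adjusted away, a paired test on 2.5 points with SD 4.12 would have power 0.28. But the one-half is an assumption with no basis in the protocol, and the unadjusted paired test keeps 0.91.
- **That the whole multiple-comparison clause fails.** Scheffé's method does control familywise error; only Duncan's test does not.

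**Conclusion.** The concern holds in this limited form. The elimination rule, the unprotected drug and group terms, and the lack of a decisive test are plain in the text for both studies. If any retained drug or group term may be claimed, error at 0.01 is about 3–5% (BI-type) to 6–8% (TME), and 24–27% in TME at the 0.05 retention threshold. These sizes rest on the simulated model structures and assumed correlations; Monte Carlo error is about 0.2–0.8 percentage points. The TME results also assume independent steps within a session. With an assumed within-session correlation of 0.5, a subject-only random effect gives about 11–13% for the drug main effect at 0.01 even without elimination, which is a separate weakness.

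The adjustment problem depends on infusion-time SHA and PPT being meant and on naloxone changing them. The 12–41% loss is illustrative. The mismatch between models and outcomes needs no assumption. The planned number of 14 is unaffected.

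**What to change.** - Delete the P > 0.05 elimination rule for both primary outcomes.
- Name one prespecified decisive test at 0.01 per study. TME: the naloxone–placebo contrast in SPID, by the two-sided paired test that reproduces N = 14. BI: the high- versus low-sensitizer contrast in ΔSHA.
- Exclude infusion-time SHA and PPT from the TME primary model. If baseline values were intended, say so. Remove SHA from the factors of the BI model.
- Move HADS, PCS and the interactions to an exploratory model with a fixed set of terms.
- Drop Duncan's test. Scheffé's method may stay, or Holm's procedure may be used.

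The cost is wording only: no change to sample size, visits or data collected.

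### Duncan's test at 0.01 lets the family-wise error reach about 0.02 across the three infusion steps, and the unruled choice between Duncan and Scheffé can decide the result

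*Protocol*

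**What the plan says.** Protocol section 13.2.1 (TME-participants) states: "The risk of type I error is reduced by setting a significance level of 0.01". It adds a power target ("A power of 0.90") and then the multiplicity rule: "For all statistical calculations, in which multiple comparisons are performed", "Duncan's new multiple range test or Scheffé's method, as appropriate, will be used". The data-processing section for BI-participants repeats the same sentences.

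Neither section says which method applies to which comparison, defines the set of comparisons to be protected, or makes the follow-up tests depend on a significant overall test. On timing, the protocol says: "Statistical calculations will be performed with partially un-blinded data, i.e., group A and B".

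The infusion factor has three levels ("step 1/step 2/step 3"). Section 11.1 has all TME outcomes assessed once before and three times during infusion, so outcomes that are not baseline-subtracted have four time points. Drug by step gives six means.

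**The concern.** A reader will expect a multiplicity procedure named directly after a 0.01 level to preserve that level over the comparisons it covers. Duncan's test is not built to do so: its protection loosens as the number of means grows. Scheffé's method protects against every possible contrast and is therefore strict when only a few pairwise differences matter. Allowing either, without a rule, leaves a liberal-or-conservative choice open while the data are already separated into two coded groups.

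At stake are statements about whether the naloxone effect differs between infusion steps, whether an outcome changes between time points, and which drug-by-step means differ. Under one permitted option such statements carry more error than the 0.01 suggests. Under the other, real differences are harder to show than they need be.

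**Working it through.** **Inputs from the protocol.** Level 0.01 and power 0.90 (sections 13.1.1 and 13.2.1). TME sample size stated "to be 14 (effect size 1.2"). Paired design: "the design is a placebo-controlled, randomized, double-blind, crossover study". Families of 3 means (steps), 4 (baseline plus steps) or 6 (drug by step).

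**1. The plan's own figure.** For a two-sided paired t-test, power is the probability that a noncentral t with n−1 degrees of freedom and noncentrality d√n exceeds the 0.01 critical value in absolute size. With d = 1.2 and n = 14, the critical value is 3.012 on 13 df and the power is 0.907, so 14 is reproduced. The stated range is too: d = 1.7 gives 9 and d = 1.0 gives 19. A one-sided test with d = 1.2 would give 12. The 0.01 was therefore used as the two-sided level of one paired test.

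**2. Duncan's error.** Its protection level for k means is (1−α)^(k−1). If all k means are truly equal, the family-wise error is 1 − 0.99^(k−1):

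- k = 2: 0.0100
- k = 3: 1 − 0.99² = 0.0199
- k = 4: 1 − 0.99³ = 0.0297
- k = 6: 1 − 0.99⁵ = 0.0490

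**3. Simulation and critical values.** There were 200,000 repeated-measures data sets per k, with n = 14, normal errors, equal correlation, no true differences and df = 13(k−1). Critical t and pairwise p are for the widest range.

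| Means | Duncan error | Scheffé error | Critical t, Duncan / Scheffé | Pairwise p threshold, Duncan / Scheffé |
|---|---|---|---|---|
| 3 | 0.0203 | 0.0073 | 2.898 / 3.325 | 0.0075 / 0.0026 |
| 4 | 0.0295 | 0.0048 | 2.902 / 3.603 | 0.0061 / 0.0009 |
| 6 | 0.0498 | 0.0016 | 2.944 / 4.070 | 0.0045 / 0.0001 |

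Tukey's method, for reference, gave 0.0102, 0.0099 and 0.0098. With three means, any widest difference with an absolute t between 2.898 and 3.325 is significant by Duncan and not by Scheffé. With two means all three methods share the critical value 3.012.

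**4. If a significant overall F at 0.01 were required first.** With no true differences, the simulated error of gated Duncan is 0.0103, 0.0099 and 0.0097 for 3, 4 and 6 means. When one mean truly differs, the gate opens and k−1 equal means remain, so the expected error is 1 − 0.99^(k−2):

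- k = 3: 0.0100 (simulated 0.010)
- k = 4: 0.0199 (simulated 0.019 to 0.022)
- k = 6: 0.0394 (simulated 0.038 to 0.040)

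A gate thus restores about 0.01 for three means only.

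**The case against.** Several points limit this concern, and most of them stand.

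- **The level is not called family-wise.** A reader might infer that the protocol promises 0.01 over the whole family and then breaks the promise. It does not say so; the link comes from the order of the sentences, and the sample size uses 0.01 for one test. What remains is that a multiplicity procedure is named which does not preserve the level set just before it.
- **The main contrasts are untouched.** A reader might infer that the primary conclusions run at two or three times their stated error. Section 13.1.1 takes the summed pain score at the highest obtainable step, which gives one naloxone-placebo contrast. The BI differences take the maximum over the three steps, and sensitizer status has two levels. With two means nothing is inflated.
- **A threefold excess does not apply to ΔSPID.** That outcome is already baseline-subtracted and has three steps, so its excess is twofold. The figure for four means belongs to outcomes compared over baseline and three steps.
- **The 0.05 in the same section is not a multiple-comparison level.** It is the threshold for dropping model factors. Nothing says Duncan's test would be run at it.
- **The ANOVA comes first.** If it were a gate, the three-step case would be resolved. The protocol does not state one, and with four or more means a gate is not enough.
- **A statistical analysis plan could settle the choice.** It could, and the protocol does not say that the choice is made after results are seen. But the protocol itself names the unsuitable method, so its sentence needs correcting in any case.

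It is also fair to say that a 2% family-wise error on step comparisons is modest in a study whose BI part is described as proof-of-concept.

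**Conclusion.** The concern holds in limited form. Used without a gate at 0.01, Duncan's test has a family-wise error of about 0.020 over three infusion steps, 0.030 over four time points and 0.049 over six drug-by-step means. Scheffé's pairwise error is about 0.007, 0.005 and 0.002. The two permitted methods can disagree on the same data, and the protocol gives no rule for choosing.

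These figures assume no true differences, 14 participants, and normal data with equal correlation between steps; the Duncan formula itself does not depend on the sample size. The damage is confined to step-wise, time-point and drug-by-step claims. The correction is worth making because the sentence governs both studies and is cheap to replace.

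**What to change.** In the data-processing sections for both TME- and BI-participants, delete the Duncan-or-Scheffé choice. Name one family-wise-controlling method for each family, and fix both before anyone sees group-coded data:

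- **At which steps naloxone acts:** paired naloxone-placebo comparisons at the three infusion steps, Holm-adjusted at overall 0.01, or tested in a fixed sequence from the highest step, each at 0.01. Comparing ΔSPID between steps would not answer this question; it asks whether the effect differs by step.
- **Between-step or time-point comparisons, if wanted:** Holm or Tukey at overall 0.01, with the means in the family listed.

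The cost is a sentence or two in each section and slightly stricter thresholds than Duncan's. Holm's smallest p-value must meet 0.01/3 = 0.0033, against Duncan's 0.0075 for the widest of three means. The fixed sequence leaves the highest-step contrast at the full 0.01, so the power of 0.907 behind the sample size of 14 is kept; Holm could give up some power there.
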